## **7.9 Reporting Procedures for Serious Adverse Events**

All SAEs must be reported to North Bristol NHS Trust Research and Innovation (NBT R&I) within 1 working day of discovery or notification of the event. NBT R&I will perform an initial check of the report, request any additional information and ensure it is reviewed. All SAEs must be reviewed at the next Trial Safety Group meeting. All SAE information must be recorded on an SAE form and faxed or emailed to NBT R&I. Additional information received for a case (follow-up or corrections to the original case) need to be detailed on a new SAE form and faxed or emailed to NBT R&I.

## **7.10 SUSAR Reporting**

The PI will support NBT R&I to report all SUSARs to the MHRA, the local REC, and the manufacturer of the drug. Fatal or life-threatening SUSARs must be reported within 7 days and all other SUSARs within 15 days. The PI will inform all study staff concerned of relevant information about SUSARs that could adversely affect the safety of participants.

## **7.11 Annual Safety Reports**

In addition to the expedited reporting above, the PI shall submit once a year throughout the clinical trial or on request a safety report to the MHRA, REC, and manufacturer of the drug.

## **8 STATISTICS**

A full, detailed statistical analysis plan (SAP) will be prepared and completed before study data are unblinded.

### **8.1 Description of Statistical Methods**

The primary analysis will compare the active group with placebo using a mixed-effect model with repeated measures (MMRM) to compare the active group with placebo in all randomised Primary Study Stage subjects. The response variable will be the primary endpoint: the percentage change from baseline in the motor UPDRS in the OFF-state at 9 months, with motor UPDRS in the OFF-state at baseline as a covariate. In addition, sensitivity analyses employing different study populations or baseline values and an analysis of covariance model will be performed.

Secondary and supplementary PD outcome variables based on percent change from baseline and change from baseline will be analysed similarly to the primary endpoint for continuous variables and with corresponding categorical analyses for categorical variables.

Descriptive statistics will be presented for all endpoints by treatment group supporting the primary and secondary analyses. No multiplicity adjustments are planned for this phase II study, and all hypothesis tests will be run with 2-sided  $\alpha = 0.05$ . Details of all analyses will be provided in the SAP.

Safety data will be presented descriptively, by treatment group, with standard Medical Dictionary for Regulatory Activities (MedDRA) coded AE and SAE frequency and incidence tables as well as shift tables for clinical laboratory parameters.

### **8.2 Number of Participants**

The endpoint used as the basis for the sample size calculation of the Primary Study Population is the percentage change from baseline to 9 months in motor UPDRS in the practically defined OFF state. Assuming a standard deviation of 20%, a 2-sided type I error of 5%, a power of 80% and a difference of 20 points in % change in motor UPDRS from baseline (e.g., a response in the active group of 25% and a placebo response of 5% or a response in the active group of 35% and a placebo response of 15%), a total of 34 evaluable subjects, randomised on a 1:1 basis, will be required to

complete the study. As a point of reference, a 5% placebo response rate was seen in the previous phase II study [11]. To compensate for a potential 5% loss of subjects for the evaluation of the primary endpoint at 9 months (with last observations at earlier time points carried forward to 9 months), a total of 36 subjects will be randomised in the Primary Study Stage and will constitute the primary analysis population.

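### The sample-size section carries last observations forward to 9 months for the primary endpoint, and this is not reconciled with the MMRM named as the primary analysis

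*Protocol*

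**What the plan says.** Protocol section 8.1 (Description of Statistical Methods) compares active with placebo "using a mixed-effect model with repeated measures (MMRM"). The response is percentage change from baseline in OFF-state motor UPDRS at 9 months, with the baseline score as covariate. It lists sensitivity analyses, among them an analysis of covariance. It does not mention carrying values forward.

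Protocol section 8.2 (Number of Participants) arrives at "a total of 34 evaluable subjects, randomised on a 1:1 basis". It then adds subjects: "To compensate for a potential 5% loss of subjects for the evaluation of the primary endpoint at 9 months", followed in parentheses by "with last observations at earlier time points carried forward to 9 months". The sentence ends: "a total of 36 subjects will be randomised in the Primary Study Stage and will constitute the primary analysis population".

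Three other places bear on the point:

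- Section 5.7.1.1 schedules post-baseline UPDRS ratings at Weeks 8, 16, 24, 32 and 40.
- Sections 5.6.5 and 5.10 ask subjects who stop early to undergo the Week 40 assessments where possible.
- Section 8.5 leaves the handling of missing data to the SAP, which is not at hand.

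**The concern.** The only missing-data rule that the protocol states for the primary endpoint is the one in the section 8.2 parenthesis. It is attached to the evaluation of that endpoint in the population that will be analysed, not to the sensitivity ANCOVA. It is also a different kind of rule from the model in section 8.1. An MMRM fitted by likelihood takes each subject's observed visits and, under missing-at-random, estimates the Week 40 difference without filling anything in. LOCF fills in a fixed Week 40 value for anyone who stopped.

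With any dropout the two can give different estimates. LOCF also treats the filled-in scores as if they had been observed, so the standard error is too small. Early scores on which to act will exist, because early stoppers are to be assessed when they stop.

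The bias can run either way. If active subjects stop before the effect is complete, or placebo subjects stop before worsening, LOCF shrinks the difference. If active subjects stop before losing an early gain, LOCF enlarges it. With 18 subjects per arm, a handful of such values can matter.

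**Working it through.** **Inputs from section 8.2**

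- "a 2-sided type I error of 5%, a power of 80"%
- "Assuming a standard deviation of 20"%
- "a difference of 20 points in % change in motor UPDRS from baseline"
- 34 evaluable, allocated 1:1; 5% loss; 36 randomised (18 per arm)

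**Step 1: reproduce the plan's sample size.**

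Normal approximation: n per arm = 2 × (1.960 + 0.842)² × (20/20)² = 15.7, so 16 per arm and 32 in total.

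Exact two-sample t, with noncentrality 20 / (20 × √(2/n)):

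- 16 per arm: power 78.1%
- 17 per arm: power 80.7%
- 18 per arm: power 83.0%

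The smallest size that reaches 80% is 17 per arm, which is the plan's 34. Inflating for loss, 34 / (1 − 0.05) = 35.8, so 36. Conversely, 36 × 0.95 = 34.2. Both stated figures reproduce, and neither calculation uses LOCF or MMRM. Removing the parenthesis therefore leaves them unchanged.

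**Step 2: set the two statements side by side.**

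| | Section 8.1 (MMRM) | Section 8.2 (parenthesis) |
|---|---|---|
| Data used for a subject last rated at Week 16 | Weeks 8 and 16, as observed | Week 16 score, entered as the 9-month score |
| Imputation | None needed | Single, fixed value |
| Main assumption | Missing at random | No change after the last rating |

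**Step 3: what carrying forward would do to the difference.** The protocol gives no dropout pattern and no time course of effect, so this step rests on assumptions. Let a proportion p drop out equally in both arms, and let their carried-forward values hold a fraction f of the 20-point effect. Analyse all 36 and keep the SD at 20. The expected difference is

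D = 20 × [1 − p × (1 − f)]

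and power is from the exact t with 18 per arm.

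| Dropout p | f = 0 | f = 0.25 | f = 0.50 | f = 0.75 |
|---|---|---|---|---|
| 5% | 19.00 (79.1%) | 19.25 (80.1%) | 19.50 (81.1%) | 19.75 (82.1%) |
| 10% | 18.0 (74.6%) | 18.5 (76.9%) | 19.0 (79.1%) | 19.5 (81.1%) |
| 20% | 16.0 (64.5%) | 17.0 (69.8%) | 18.0 (74.6%) | 19.0 (79.1%) |

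Cells show expected difference in points, with power in brackets. The shift from 20 is 0.25 to 1 point at 5% loss, 0.5 to 2 points at 10%, and 1 to 4 points at 20%. An f above 1 (an early gain later lost) would put D above 20, which is the bias in the other direction.

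These figures compare LOCF with full follow-up at the planned effect. They are not a simulated gap between LOCF and MMRM estimates, and they do not quantify the loss in standard error.

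**The case against.** The strongest reply is that the protocol has already settled the matter. Section 8.1 names a single primary method, the carry-forward words are an aside in a sample-size paragraph, and section 8.5 hands missing data to the SAP. This stands in part. A reader might infer that two rules govern the primary analysis, or that section 8.2 fixes LOCF as the primary method. The text does not support that, since the parenthesis specifies no model or estimator. But deferring detail to the SAP does not withdraw a rule that the protocol states. What remains is an inconsistency in the text, not a missing detail.

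Four other stronger readings are tempting and should be resisted:

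- **That the step from 34 to 36 is itself wrong.** Section 8.2 is not clear about who counts as lost once earlier values are carried forward. But the 5% can be read as subjects with nothing usable, and allowing for missing Week 40 values is ordinary planning under an MMRM too.
- **That the sponsor could choose between results after the fact.** The introduction to section 8 requires the SAP to be complete before unblinding, and section 8.6 requires later changes to be identified in the study report. These limit that risk.
- **That a definite bias can be calculated.** If the effect built linearly, 16/40 × 20 = 8 points would be present at Week 16, and one active subject carried forward from there would cost 12/18 = 0.67 points. The linear build-up and the dropout in the active arm only are both suppositions, because the protocol gives no time course.
- **That placebo subjects stopping before they worsen would inflate the effect.** They would make placebo look better and so move the difference toward the null.

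It can also be said that carry-forward might be meant for the sensitivity ANCOVA. That is possible, but the protocol does not say so.

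**Conclusion.** The point holds as an unreconciled statement. Section 8.2 describes carrying forward for the primary endpoint, and the primary analysis named in section 8.1 neither needs nor mentions it. It should be corrected, but it does not undermine the design: the sample size, power calculation, endpoint, population and primary model all stay as they are.

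If the parenthesis were applied, the expected difference would move by at most about 1 point of 20 at the planned 5% loss, and by 1 to 4 points at 20% loss. This assumes equal dropout in both arms, carried-forward values holding 0 to 75% of the effect, and an unchanged SD of 20. Other dropout patterns could move the difference in the opposite direction. So the consequence is small at the loss the plan expects, and material only if loss is well above it.

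**What to change.** Delete the carry-forward parenthesis from section 8.2. In its place, state that 36 subjects are randomised so that about 34 have an observed Week 40 value, and that the primary analysis is the MMRM of section 8.1 on all observed post-baseline visits, without LOCF. If the sponsor wants to keep LOCF, name it as a sensitivity analysis using the ANCOVA already foreseen in section 8.1. Make the SAP wording match before unblinding.

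The cost is one sentence in the protocol and the corresponding line in the SAP. No number in section 8.2 changes.

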### **8.3 Level of Statistical Significance**

The study design assumes a 2-sided type I error of 5%, equating to a p-value of  $< 0.05$ , in all analyses.

### **8.4 Criteria for the Termination of the Trial**

The study will be monitored by an independent DMC established by the sponsor or designee and governed by a separate charter. The responsibilities of the DMC will include performing the safety analysis after the last pilot subject has completed 3 months of treatment. The DMC may recommend termination of the trial at any point for safety reasons.

This study may be terminated by the Sponsor. The study may also be terminated prematurely at any time when agreed to by both the PI and the Sponsor as being in the best interests of subjects, and justified on either medical or ethical grounds. In terminating the study, the Sponsor and the PI will ensure that adequate consideration is given to the protection of the subjects' interests.

### **8.5 Procedure for Accounting for Missing, Unused, and Spurious Data**

Methods for handling missing or incomplete data will be described in the SAP.

### **8.6 Procedures for Reporting any Deviation(s) from the Original Statistical Plan**

Changes to the SAP planned before study data are unblinded will be documented in a revised SAP or SAP addendum or amendment issued before unblinding. Any changes to the planned analyses made after unblinding will be clearly identified in the final Clinical Study Report.

## 8.7 Inclusion in Analysis

The primary analysis will be conducted after all Primary Study Stage subjects have reached the 9-month endpoint.

The primary analysis population will include all subjects randomised to the study in the Primary Study Stage of the study. The primary analysis will follow the ITT principle, with all subjects randomised in the Primary Study Stage included and grouped according to randomised treatment (regardless of treatment received). Subjects randomised in the Pilot Stage will not be included in the ITT population for the primary analysis as the treatment parameters may be altered during this phase.

In addition, efficacy analyses will be repeated on the ITT Overall Population comprising all randomised Primary Stage subjects and all randomised Pilot Stage subjects and on the Per Protocol Population, comprising all subjects treated in the study (i.e., including subjects randomised in the Pilot Stage) and without major protocol violations. Misrandomisations constitute major protocol violations.

The Safety Primary Population will comprise all Primary Study Stage subjects who received at least one dose of study medication, with subjects grouped according to treatment actually received. All safety analyses will be performed on the Safety Primary Population. More limited analyses will be performed for the Safety Overall Population comprising all subjects (both Pilot and Primary Study Stage) who received at least one dose of study medication, with subjects grouped by treatment actually received. Safety data for Pilot Stage subjects will be provided and evaluated via individual data listings. Pre-treatment AEs will be analysed in the Safety Enrolled Population comprising all enrolled subjects (Primary Study Stage and Pilot Stage subjects combined).

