#### **5.1.1 Pilot Stage**

The purpose of the Pilot Stage is to ensure the safety of the surgical technique and study drug administration and, if necessary, optimise these prior to initiating the Primary Study Stage. Six subjects with PD of moderate severity will be randomised in a 2:1 allocation (total of 4 subjects receiving active GDNF and 2 subjects receiving placebo) to receive infusions of GDNF or placebo every 4 weeks in a double-blind fashion for 9 months (10 infusions; last infusion at Week 36). A safety review of these 6 subjects will be performed by both the independent Data Monitoring Committee (DMC) and the Medicines and Healthcare Products Regulatory Agency (MHRA) after the last pilot subject has completed 3 months of treatment. While the Pilot Stage is primarily aimed at confirming the safety of the study treatments and procedures and meeting regulatory requirements as articulated by the MHRA, it also serves to potentially optimise options for handling infusions in subjects allowing minor modifications of procedures in response to any surgical, technical, infusion, imaging or logistical issues that may be identified. Subjects randomised in the Pilot Stage will be analysed together with the subjects randomised in the Primary Study Stage as part of the safety and supplementary efficacy analyses but will not be included in the primary efficacy analysis.

**Figure 7 Study Schema**[figure not shown]

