### 5.1.2 Primary Study Stage

Following the safety review by both the DMC and MHRA after the last pilot subject has completed 3 months of treatment, 36 additional subjects with PD of moderate severity will be randomised in a 1:1 allocation to receive infusions of either GDNF or placebo

every 4 weeks in a double-blind fashion for 9 months (10 infusions; last infusion at Week 36) in the Primary Study Stage. The primary, secondary and other applicable endpoints of the study will be determined when subjects randomised in the Primary Study Stage have completed (or had the opportunity to complete) 9 months of double-blind treatment. As the delivery technique may be slightly modified during the Pilot Stage, only subjects randomised in the Primary Study Stage will be included in the analysis of the primary and secondary endpoints.

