#### **5.5.4 Randomisation and Preparation of Study Drug**

Randomisation will be administered centrally via the Bristol Randomised Trials Collaboration (BRTC) Clinical Trials Unit (CTU) after the inclusion/exclusion criteria have been confirmed and the post-surgery randomisation criteria are met as confirmed by the PI. Eligible subjects in the Pilot Stage will be randomised in a 2:1 ratio to achieve 4 active and 2 placebo subjects. In the Primary Study Stage, eligible subjects will be randomised in a 1:1 ratio to the active or placebo arm, using a blocked randomisation scheme with a block size of 6. The randomisation sequence will be based on a computer programme, which will allocate a random number that determines the study drug (GDNF or aCSF) dispensed by the pharmacy whilst maintaining concealment of allocation.

All study drug will be prepared by an unblinded pharmacist at the study site based on the randomisation. Ready to use preparations of GDNF or aCSF will be provided to the PI or designee in identical containers identifiable only by codes unknown to the PI or any other study staff. Drug preparation guidelines are provided in a separate pharmacy manual.

In the event that there is a delay in randomization which results in the baseline assessment occurring more than 24 weeks after screening visit 2, efficacy outcome measures completed during screening but not repeated at baseline must be repeated

prior to the baseline visit unless they have a significant practice effect. The list of measures to be repeated includes:

- Stroop
- Reaction time
- FrSBe
- UPPS-P
- PD NMSS
- PDQ-39
- EQ-5D
- SNAQ
- UPSIT
- QUIP

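### The only Per Protocol set takes in the Pilot Stage, so it is not a subset of the primary ITT population, and its comparison with the primary result mixes adherence with stage

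*Protocol*

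**What the plan says.** Section 8.7 gives the reason for leaving the Pilot Stage out of the primary analysis: "Subjects randomised in the Pilot Stage will not be included in the ITT population for the primary analysis as the treatment parameters may be altered". Section 5.1.2 gives a similar reason and applies it to the secondary endpoints as well: "As the delivery technique may be slightly modified during the Pilot Stage, only subjects randomised in the Primary Study Stage will be included".

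Section 8.7 then repeats the efficacy analyses on two further sets. One is the "ITT Overall Population comprising all randomised Primary Stage subjects and all randomised Pilot Stage subjects". The other is the "Per Protocol Population, comprising all subjects treated in the study (i.e., including subjects randomised in the Pilot Stage) and without major protocol violations". No Per Protocol set confined to the Primary Study Stage is defined. For safety, the same section defines both a Primary and an Overall population.

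Section 5.1.1 declares the role of pooling: Pilot subjects "will be analysed together with the subjects randomised in the Primary Study Stage as part of the safety and supplementary efficacy analyses".

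On allocation, Section 5.5.4 states: "Eligible subjects in the Pilot Stage will be randomised in a 2:1 ratio to achieve 4 active and 2 placebo subjects". The Primary Study Stage is allocated 1:1. For the primary model, Section 8.1 specifies percentage change from baseline "with motor UPDRS in the OFF-state at baseline as a covariate", and it leaves the details of all analyses to the SAP.

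**The concern.** A Per Protocol analysis is normally read against the ITT analysis to see whether departures from the protocol move the result. That reading needs the Per Protocol set to lie inside the ITT set. Here it does not lie inside the primary ITT population: violators leave, and subjects whose delivery may have differed come in. If the two results disagree, the reader cannot tell from that comparison whether adherence or stage is responsible.

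The current text shows that the stages can differ. The Pilot Stage exists partly so that procedures can be adjusted (Section 5.1.1). Pilot subjects are imaged after every infusion, whereas Primary Study Stage subjects have no interim MRI unless it is clinically required (Sections 5.5 and 5.6.4). Infusion time may depend on what post-infusion imaging shows (Section 6.3).

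There is a second, conditional issue. Pooling a 2:1 stage with a 1:1 stage ties stage to arm. A pooled model without a stage term would carry part of any stage difference into the treatment estimate.

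**Working it through.** **Nesting of the sets (planned numbers, before exclusions)**

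- Primary ITT: 36 Primary Study Stage subjects (18 + 18).
- ITT Overall: 36 + 6 = 42.
- Per Protocol: at most 42, both stages, less untreated subjects and major violators.

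Per Protocol lies within ITT Overall but not within the primary ITT population. With no violators at all it would hold 42 subjects against 36.

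**The plan's own figures.** Section 8.2 assumes SD 20, a difference of 20 points, 2-sided 5% and 80% power. A two-sample t-test gives 80.7% power at 17 per arm and 78.1% at 16, so 34 evaluable subjects is reproduced. Then 34/0.95 = 35.8, which rounds up to 36. The same SD is used below, with a t-test on the Week 40 percentage change as an approximation to the planned repeated-measures model.

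**Stage imbalance in the pooled arms**

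- Active: 18 + 4 = 22, of whom Pilot 4/22 = 18.2%.
- Placebo: 18 + 2 = 20, of whom Pilot 2/20 = 10.0%.
- Imbalance: 0.182 − 0.100 = 0.082.

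**Bias without a stage term.** Let D be the Pilot-minus-Primary difference in mean response common to both arms. The documents give no value, so D is an assumption. Bias = D × (4/22 − 2/20). The type I error comes from 100,000 simulated trials per value of D.

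| Assumed D (points) | Bias (points) | Share of the 20-point design effect | Two-sided type I error |
|---|---|---|---|
| 5 | 0.4 | 2% | 5.1% |
| 10 | 0.8 | 4% | 5.0% |
| 20 | 1.6 | 8% | 4.5% |
| 40 | 3.3 | 16% | 3.3% |

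The unadjusted standard error is 20 × √(1/22 + 1/20) = 6.18 points. Two-sided error is not inflated, because the stage difference also widens the within-arm spread. Error in the direction of the bias rises from 2.5% to at most about 3.5%. A 5-point bias would need D = 5/0.0818, about 61 points.

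**With a stage term.** The within-stage weights are 18 × 18/36 = 9 and 4 × 2/6 = 1.33. The standard error is 20/√10.33 = 6.22, and the bias from a common D is zero. Power at a 20-point effect moves from 88.5% to 88.0%.

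**What a stage term does not remove.** Suppose the treatment effect itself differs by 10 points in the Pilot Stage. The pooled estimate then shifts by 10 × 4/22 = 1.8 points without the term and by 10 × 1.33/10.33 = 1.3 points with it.

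**Per Protocol within the Primary Study Stage.** With at most 18 per arm, power at the design effect is at most 83.0%.

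**The case against.** The strongest reply is that ITT Overall supplies the missing step. Going from primary ITT to ITT Overall only adds the Pilot subjects; going from ITT Overall to Per Protocol only removes untreated subjects and violators. Each step changes one thing, so the effect of adherence can be read there. This stands, and it limits the point to the direct comparison of Per Protocol with the primary result. It does not supply an adherence check within the population on which the trial's conclusion rests.

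Some stronger readings are tempting and are not supported:

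- A reader might infer that the pooled analyses have no stage term and are therefore confounded. The covariate sentence in Section 8.1 describes the model for Primary Study Stage subjects only, where stage is constant and no such term could appear. Detail is deferred to the SAP. Bias would need both an unadjusted model and a real stage difference, and for plausible differences it is small.
- A reader might treat pooling in ITT Overall as a contradiction. It is openly declared supplementary.
- A reader might take the Per Protocol result to be the principal check on the primary one. No section says so. Section 8.1 plans several sensitivity analyses, including other baseline values and an analysis of covariance.
- A reader might infer from the amendment history that Pilot subjects received a different regimen. That history describes superseded text and does not show which Pilot subjects, if any, were affected. The current Section 6.3 gives one regimen for both stages, and Section 5.1.2 speaks only of slight modification.

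**Conclusion.** The point holds for the Per Protocol definition, which is fixed in Section 8.7 and does not depend on the SAP. The only Per Protocol set is not a subset of the primary ITT population, so a difference between their results mixes adherence with stage. The omission looks unintended, since ITT and safety each have a Primary and an Overall version and Per Protocol does not. The supplementary endpoints in Section 5.2.3 name the overall ITT population but no Pilot-inclusive Per Protocol analysis.

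The stage-term part is a conditional clarification. If the term were left out, the leakage would be 8.2% of a common stage difference: 0.8 to 1.6 points for an assumed 10 to 20 points, against a standard error of about 6.2. This rests on the planned arm sizes before exclusions (22 and 20), SD 20, and a stage difference equal in both arms. Actual Per Protocol counts are unknown.

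Severity is minor. Only supplementary and sensitivity analyses are affected; the primary and secondary analyses are confined to the Primary Study Stage.

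**What to change.** In Section 8.7 and the SAP:

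1. Define a Per Protocol Primary population: Primary Study Stage ITT subjects who were treated and had no major violation. Name it as the adherence sensitivity check on the primary result.
2. Keep the Pilot-inclusive version as a supplementary Per Protocol Overall population, to be read against ITT Overall.
3. State that every efficacy analysis pooling the two stages includes stage (Pilot or Primary) as a fixed effect, matching the two randomisation schemes. Add that this does not correct for a treatment effect that differs by stage. If the SAP already has the term, a cross-reference is enough.

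The cost is a wording change, which Section 8.6 allows before unblinding. The Per Protocol Primary set has at most 6 fewer subjects than the present Per Protocol set. The stage term uses one degree of freedom and moves the pooled standard error from 6.18 to 6.22.

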### **5.2.5 Safety Endpoints**

- Frequency of device-related adverse events (AEs) during the study period
- Frequency of treatment-emergent AEs (all treatment-emergent AEs and treatment-emergent AEs related to study drug) during the study period.
- Frequency of dyskinesias, falls, adverse changes in mood, and impulsivity reported as treatment-emergent AEs during the study period (AEs of special interest).
- Change from baseline in the Questionnaire for Impulsive-Compulsive Disorders in Parkinson's Disease (QUIP) every 8 weeks.
- Change from baseline in the Montreal Cognitive Assessment (MoCA) after 9 months of double-blind treatment.
- Change from baseline in the Mattis Dementia Rating Scale (MDRS) after 9 months of double-blind treatment.
- Adverse changes in MRI findings as captured by AE reporting.
- Frequency of subjects with anti-GDNF antibodies during the study.
- Results of routine laboratory blood tests (haematology, serum chemistry) and urinalysis performed at baseline and at intervals during the trial.

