#### **5.3.4 Post-Surgery Randomisation Criteria**

In order to be eligible for entry into the double-blind period of the study, subjects must meet the following criteria after undergoing surgery:

1. No relevant sequelae from catheter implantation such as clinically significant intracerebral trauma, haemorrhage, or infection.
2. Total distribution volume providing at least 40% volume coverage of a predefined volume of interest (posterior two thirds of the dorsal half of the putamen) in each putamen, as confirmed by the PI on the basis of the MRI scan taken within 2 hours post-test infusion of diluent at the end of the healing period. T2-weighted, FLAIR or T1-weighted MRI scans (Primary Study Stage subjects only) can be used for this assessment.

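### No safety population is defined by implantation, so device-related AE frequency is either selected through the dosing rule or split at first dose across two denominators

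*Protocol*

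**What the plan says.** The first safety endpoint in section 5.2.5 is "Frequency of device-related adverse events (AEs) during the study period". Section 7.8 records AEs from first consent to the Week 40 visit, with relatedness to medication or device, so surgery and healing lie inside that period.

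Section 8.7 names three safety sets:

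- **Safety Primary.** "The Safety Primary Population will comprise all Primary Study Stage subjects who received at least one dose of study medication". This is the lead set: "All safety analyses will be performed on the Safety Primary Population".
- **Safety Overall.** Dosed subjects from both stages, for which a reduced set of analyses is planned.
- **Safety Enrolled.** "Pre-treatment AEs will be analysed in the Safety Enrolled Population comprising all enrolled subjects", both stages combined.

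Entry to the double-blind period is conditional on section 5.3.4. Its first criterion is "No relevant sequelae from catheter implantation such as clinically significant intracerebral trauma, haemorrhage, or infection". Its second is at least 40% coverage of the volume of interest in each putamen.

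On the Pilot Stage, section 5.1.1 pools the two stages for safety as well as for supplementary efficacy: "Subjects randomised in the Pilot Stage will be analysed together with the subjects randomised in the Primary Study Stage as part of the safety". Section 5.2 also includes Pilot subjects in the safety analysis. Section 8.7 gives the pooled set the reduced analyses and adds: "Safety data for Pilot Stage subjects will be provided and evaluated via individual data listings".

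**The concern.** Device risk begins at implantation, about 8 weeks before the first dose (section 5.5). A frequency for it needs everyone exposed to the device in the denominator, and no named set is defined that way. Membership of the two dosed sets depends partly on the outcome being counted, because a serious enough unresolved implantation event prevents dosing. The only set that holds those subjects is assigned pre-treatment events alone, over a denominator that the protocol does not define.

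The system is a customised arrangement of four microcatheters and a skull-mounted transcutaneous port (section 6.2), and section 5.1.1 gives the safety of the surgical technique as a purpose of the Pilot Stage. The risk per implanted subject is a figure that a later trial or a patient would need, and the planned sets do not produce it.

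**Working it through.** **Planned numbers.** The Primary Study Stage size reproduces. For a 20-point difference, SD 20, two-sided 5% and 80% power, the exact two-sample t-test gives 16.7, so 17 per arm and 34 evaluable; 34/0.95 = 35.8, so 36 randomised. With 6 Pilot subjects, at most 36 + 6 = 42 are dosed, of whom 18 + 4 = 22 are on GDNF. The protocol plans no number implanted or enrolled.

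**Which set holds which device events.**

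| Subject | Safety Primary / Overall | Safety Enrolled |
|---|---|---|
| Implanted, dosed | Yes (Overall only, if Pilot) | Yes, pre-treatment events only |
| Implanted, stopped by 5.3.4 | No | Yes, pre-treatment events only |
| Never implanted | No | Depends on the meaning of enrolled |

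Two readings of 8.7 are possible. If the dosed-set table counts all device events in dosed subjects, including those before first dose, the rate is selected by 5.3.4. If it counts only events after first dose, device events are split between two tables. A subject with events on both sides then appears in both, so the tables cannot be added to give a per-implanted rate.

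**Illustration. All counts are assumed except 42, the planned maximum dosed.** Let d = 4 dosed subjects have a device-related AE, k subjects be implanted but stopped by sequelae (each with a device-related AE), and s be enrolled but never implanted.

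- Dosed rate = d/42
- Implanted rate = (d + k)/(42 + k)
- Enrolled rate = (d + k)/(42 + k + s). This is an upper limit, because 8.7 gives that set pre-treatment events only.

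| k | Dosed | Implanted | Enrolled, s = 0 | Enrolled, s = 20 | Enrolled, s = 40 |
|---|---|---|---|---|---|
| 0 | 4/42 = 9.5% | 4/42 = 9.5% | 9.5% | 4/62 = 6.5% | 4/82 = 4.9% |
| 1 | 9.5% | 5/43 = 11.6% | 11.6% | 5/63 = 7.9% | 5/83 = 6.0% |
| 2 | 9.5% | 6/44 = 13.6% | 13.6% | 6/64 = 9.4% | 6/84 = 7.1% |
| 4 | 9.5% | 8/46 = 17.4% | 17.4% | 8/66 = 12.1% | 8/86 = 9.3% |

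The dosed rate does not respond to k at all and lies below the implanted rate whenever k > 0. With s = 0 the enrolled and implanted denominators coincide and nothing is diluted.

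**Pilot wording.** Sections 5.1.1 and 5.2 put Pilot subjects into the safety analysis without restriction. Section 8.7 restricts the pooled analyses and relies on listings for the Pilot Stage. Pilot subjects are 6/42 = 14.3% of planned dosed subjects and 4/22 = 18.2% of planned GDNF subjects.

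**The case against.** Much of the case on the other side stands.

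- **Surgical events are not lost.** A reader might infer that they vanish from the analysis. They do not: they are recorded from consent and analysed as pre-treatment AEs in Safety Enrolled, serious events are reported and reviewed individually (7.9), and a DMC monitors the trial.
- **Dilution is conditional.** Enrolled is not defined in the protocol, and the SAP may define it. If it means entry into the surgery and healing periods, it is close to implanted.
- **The sequelae rule is narrower than it looks.** Section 5.5.3 allows a longer healing period and surgical replacement of catheters, so a subject whose complication resolves can still be randomised and dosed. Only those who remain ineligible drop out of the dosed sets.
- **Drug safety is not confined to 18 GDNF subjects.** A reader might infer this from the lead set, but Safety Overall includes the 22 planned.
- **Objective 4.2 is not contradicted.** It names the pilot cohort and the full study population. Listings and the DMC/MHRA review serve the first; Safety Overall serves the second in reduced form.
- **Keeping the stages apart has a reason.** Delivery could change during the Pilot Stage, allocation was 2:1, and monitoring was heavier: real-time MRI, a stay of at least 22 hours after the first infusion, and MRI after every treatment.

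What these points do not supply is a set whose denominator is implanted subjects and whose window runs from surgery to Week 40. Defining enrolled as implanted would repair the denominator, but not the restriction of that set to pre-treatment events.

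**Conclusion.** The point holds as a gap in the stated analysis sets. By rule, the dosed sets omit subjects stopped by unresolved implantation sequelae or inadequate coverage, so their device-related AE frequency is biased downward if any such subjects exist. This assumes that the sequelae are recorded as device-related AEs; for subjects stopped only by coverage, it depends on whether the catheter failure was recorded as an AE. The size cannot be fixed from the protocol. In the illustration, with 0 to 4 such subjects, the implanted rate runs from 9.5% to 17.4% while the dosed rate stays at 9.5%. The change is worth making because it is cheap and uses data already collected.

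The Pilot Stage wording is a smaller, separate inconsistency between 8.7 and sections 5.1.1 and 5.2. Keeping Safety Primary as the lead set for drug safety is defensible, given the differences between the stages.

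**What to change.** Add to section 8.7 and the SAP a Safety Implanted Population: all subjects in whom implantation was started, both stages. Use it as the denominator for device- and procedure-related AEs from surgery to end of study, shown by stage and overall, and name it as the set that carries the first endpoint in 5.2.5. Define enrolled in the same place.

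Separately, reword 8.7 or sections 5.1.1 and 5.2 so that they agree on which safety analyses pool the Pilot subjects and which use listings only.

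The cost is protocol and SAP wording and a few more tables, with no new visits. Never-randomised subjects have no treatment arm and need their own column. Section 7.8 records relatedness to medication or device but not to the operation, so procedure-related events would have to be identified by medical review before unblinding.
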